**PREPARED BY:**

**[name] ([name])**

**SUPERVISOR:**

**DR. [name]**

**CO-SUPERVISORS:**

**PROF. DR. [name]**

**DR. [name]**

**DR. [name]**

## 1.0 INTRODUCTION

The primary goal of occupational therapy is to enable people to participate in the activities of daily living (ADLs) including the ability to work (Desiron et al. 2011).

Work-related hand injuries contributed to 24.9% of all industrial accidents seen at the emergency departments and orthopaedic clinics in Malaysia (Al-Husuny et al. 2012). Approximately 98.6 % of workers with traumatic hand injuries returned to work after a median absence of 45.5 days (Oberfeld et al. 2015).

Wrist joint is a joint with high activity frequencies and high functional requirements (Weimer et al. 1999). The wrist is divided into three major joint articulations, namely the distal radioulnar joint, the radiocarpal joint and the midcarpal joint (Berge 1996; Kawamura & Chung 2007). It consists of eight carpal bones interposed between the forearm (distal radius and ulna) and the bases of the metacarpals (Berger 1996; Calfee et al. 2010). The carpal bones are categorized as a proximal row and distal row based on their kinematics during wrist motions (Berger1996; Kijima & Viegas, 2009; Calfee et al. 2010). The proximal row consists of the scaphoid, lunate, triquetrum, and pisiform while the distal row consists of the trapezium, trapezoid, capitate, and hamate (Berger, 1996; Kawamura & Chung, 2007; Kijima & Viegas, 2009; Calfee et al. 2010). The distal radioulnar joint (DRUJ) consists of the ulna head, the sigmoid notch region of the distal radius, the DRUJ capsule, and the triangular fibrocartilage complex (TFCC) (Berger, 1996; Kawamura & Chung, 2007). The wrist and distal radioulnar joint combine to form an essential joint capable of providing motions with six degrees of freedom in the cardinal planes. These include flexion, extension, radial deviation, ulnar deviation, pronation, and supination that result in circumduction (Calfee et al. 2010).

Based on the wrist anatomical structures, wrist fractures may include fractures that affect the distal ends of the radius, ulna, and carpus. A distal radius fracture, commonly known as a wrist fracture, is defined by the involvement of the metaphysis of the distal radius. The fracture may or may not involve the radiocarpal joint, distal radioulnar joint, and/or the distal ulna (Mauck & Swigler 2018). Traditionally, distal

radius fractures have been described using eponyms, e.g. Colles, Smith, Barton, and Chauffeur. During the last half of the twentieth century, several classification systems for distal radius fractures have emerged which include the AO Foundation/Orthopaedic Trauma Association (AO/OTA) system (Kleinlugtenbelt et al. 2017; Mulders et al. 2017; Wæver et al. 2018), the Frykman system (Meena et al. 2014; Kleinlugtenbelt et al. 2017; Mulders et al. 2017; Wæver et al. 2018), the Melone system (Meena et al. 2014; Mulders et al. 2017), the Fernandez system (Meena et al. 2014; Kleinlugtenbelt et al. 2017; Mulders et al. 2017), and the Older system (Wæver et al. 2018). According to Wæver et al. (2018), the AO/OTA classification system seems to be most reliable for routine use while the study by Mulders et al. (2017) found high consensus among both surgeons and residents for defining the AO/OTA classification as the preferred classification system.

According to the fracture and dislocation classification compendium by the AO Foundation/Orthopaedic Trauma Association (AO/OTA) (2018), the distal end segment fractures for both the radius and ulna bones are classified into three types, namely extra articular fracture, partial articular fracture, and complete articular fracture. The distal end segment radius and ulna fractures are further classified into nine and three groups respectively. The nine groups of distal end segment radius fractures include radial styloid avulsion fracture, simple fracture, wedge or multifragmentary fracture, sagittal fracture, dorsal rim (Barton's) fracture, volar rim (reverse Barton's, Goyrand Smith II's) fracture, simple articular and metaphyseal fracture, metaphyseal multifragmentary fracture, articular multifragmentary fracture, and simple or multifragmentary metaphyseal fracture. Meanwhile, the three groups of distal end segment ulna fractures include extraarticular, styloid process fracture, simple fracture, and multifragmentary fracture.

Incidence of distal radius fracture is increasing worldwide in which one sixth of the fractures treated in emergency rooms appears to be related to distal radius (Mitchlovitz et al. 2001; MacIntyre & Dewan 2016). Majority of patients had some degrees of disability one year after distal radius fracture with 16% had moderate to very severe disability and were not working (Moore & Leonardi-Bee 2008). Patients who have high self-reported pain/disability and occupational demand at baseline have an

average of 9.2 weeks of work loss following distal radius fracture (MacDermid et al. 2007). Hand injury costs had brought cumulative economy impact not only to patients, but their family, employer, and society (Dias & Garcia-Elias 2006). As the incidence of distal radius fractures rises, the short and long term costs become apparent (Nellan et al. 2012).

Stiffness and pain (Egol et al. 2014) are common complications of distal radius fractures. Loss of range of motion (ROM) is typically due to periarticular connective tissue changes after fractures, joint injuries, and immobilization (Mitchlovitz et al. 2004). Decreased wrist flexion and/or extension after trauma or surgery can be a challenging problem (McGrath et al. 2008). The ultimate goal of restoring motion is to reduce impairments and enhance functional performance for ADLs, work, and leisure.

The rehabilitation program following distal radius fractures involves three phases: immobilization phase, mobilization phase, and strengthening phase. The fundamental goals throughout these three phases include effective edema control and pain management as well as ROM, strength, and functional restorations (Mitchlovitz et al. 2001). The most frequently used therapeutic interventions following distal radius fractures include compressive wrap with retrograde massage, heat/cold modalities, joint mobilization, electrical stimulation, continuous passive motion (CPM), soft-tissue mobilization, ultrasound, splinting, ROM and strengthening exercises, and functional training (Mitchlovitz et al. 2001). The commonly used nonsurgical interventions for ROM restoration after fracture, fracture/dislocation, joint injury, or other soft tissue injuries include home exercise program and clinic based program such as splinting and casting, joint mobilization, CPM, and therapeutic exercises (Mitchlovitz et al. 2004).

Improper rehabilitation program after wrist injury may significantly impair the overall function of the upper extremity (Garcia-Elias & Folgar 2006). Both injury and patient factors can impact the management and outcomes after distal radius fracture. Although optimal strength, ROM, and function are achievable within 3-6 months of conservative or surgical management (MacDermid et al. 2007), some patients require longer duration to complete the rehabilitative phase. According to Moore and

Leonardi-Bee (2008), there are 11% of patients endure residual moderate to very severe pain one year following distal radius fracture with 16% still experiencing ongoing disability. This signifies that there is a significant association between patient characteristics and the level of pain and disability among the distal radius fracture population.

With respect to the employability issues of the workers with wrist fractures, Lam et al. (2010) had advocated that matching treatment to the patient's stage of employment readiness appears to be a more effective approach to service provision. A timely and goals oriented treatment-matching approach in the work program will deliver better outcomes in term of cost effectiveness, employment and service quality. The Lam Assessment on Stages of Employment Readiness (LASER) has been used in the treatment-matching endeavour by assessing the patient's stages of employment readiness based on Prochaska's State of Change theory that consists of three stages, namely the Pre-Contemplation, Contemplation, and Action stages (Chan et al. 2006; Lam et al. 2010).

The application of robotic technology in facilitating upper limb movement and functional recovery training is extensive in the field of neurorehabilitation (Riener et al. 2005; Riener 2007; Wagner et al. 2011; Lo & Xie 2012; Ren et al. 2013; Maciejasz et al. 2014; Borboni et al. 2016; Zhang et al. 2017; Hsieh et al. 2018; Ferreira et al. 2018) but limited in the field of orthopaedic rehabilitation particularly in hand therapy practice. Given the current concepts of robotic intervention are focused on providing motor control/learning, practice-induced neuroplasticity, intensity, and task specific training, Hakim et al. (2017) have suggested the application of robotic intervention in orthopaedic rehabilitation with upper extremity disorders, especially those related to hand and wrist.

There are various types of robotic devices that can be used for upper limb rehabilitation, subject to their respective mechanical designs (i.e. end-effector-based or exoskeleton-based) and types of assistance provided (i.e. active, passive, haptic or coaching) (Maciejasz et al., 2014). The Single Joint Hybrid Assistive Limb (HAL-SJ) is one of the robotic devices that can be used for upper limb rehabilitation. Hybrid

Assistive Limb (HAL) is a cyborg type robot that can expand, augment, and support physical capability in order to enhance and upgrade human capabilities based on the frontier science “Cybernetics”. Cybernetics is a new domain of interdisciplinary research centered on cybernetics, mechatronics, and informatics that integrates neuroscience, robotics, systems engineering, information technology, “kansei” engineering, ergonomics, physiology, social science, law, ethics, management, economics, etc. (Sankai 2010).

The HAL is a hybrid control system that consists of a ‘Cybernetic Voluntary Control (Bio-Cybernetic Control)’ and ‘Cybernetic Autonomous Control (Cybernetic Robot Control)’. The cybernetic control system can provide suitable physical support to wearers with various conditions including both healthy persons and physically challenged persons by using the two types of algorithms as complementary controls. The Cybernetic Voluntary Control provides physical supports/actions according to the operator’s voluntary intention caused by the bioelectrical signals including muscle activity. The power units of HAL generate power assist torque by amplifying the wearer’s own joint torque estimated from his/her bioelectrical signals, and the support motions are consequently controlled. Bioelectrical signals, including myoelectricity, are useful and reliable information to estimate a human’s motion intentions because the signals are measured just before corresponding visible muscle activities. Thus, the wearer receives physical support directly by an unconscious interface using the bioelectrical signals. In contrary, the Cybernetic Autonomous Control autonomously provides a desired functional motion generated according to the wearer’s body constitution, conditions, and purposes of motion support (Sankai 2010).

The upper limb HAL-SJ is a wearable movement support robot that detects bioelectrical signals on the skin surface and assists joint movements by controlling and operating an actuator placed outside the respective joint (Otsuka et al. 2011; Kubota et al. 2018). Upper limb rehabilitation using the elbow joint HAL-SJ robotic therapy has been applied to promote elbow functions among neurological patients. Functional imaging study had shown cortical neuroplasticity activity associated with elbow movements among post-stroke patients following 20 sessions of elbow joint HAL-SJ intervention for the paretic arm in two weeks period (Saita et al. 2016). In addition,

studies had proved the safety and feasibility of the upper limb HAL-SJ application for the upper limb rehabilitation of quadriplegia patients (Kubota et al. 2018; Shimizu et al. 2017). The upper limb HAL-SJ is also proven safe and effective to be used for the rehabilitation following traumatic brachial plexus injury (Kubota et al. 2017). A newly developed wrist joint attachment to the HAL-SJ is currently available and is capable of assisting voluntary articulatory movements of the wrist joint including wrist flexion and extension as well as forearm supination and pronation.

Robotic technologies have been developed for motor rehabilitation and such robots have shown favourable results when compared with equivalent doses of usual clinical therapy (Lo et al. 2010; Novak 2018). Compared to manual therapy, robotic intervention for rehabilitation has the potential for a greater impact on impairment due to easy deployment, its applicability across of a wide range of motor impairment, its high measurement reliability, and the capacity to deliver high dosage and high intensity training protocols for a longer duration, irrespective of the skills, and fatigue level of the therapist (Huang & Krakauer 2009). Based on the understanding that the amount and intensity of exercise and the quality of motor learning are positively associated with rehabilitation outcome as aforementioned and the fact that HAL-SJ is a newly developed robotic intervention device that shares similarities on the therapeutic features provided by other robotic devices, the application of the HAL-SJ is hypothesized to provide similar positive outcome for wrist fractures. Investigating the outcome of HAL-SJ among upper limb injured workers, especially those with wrist fractures shall provide further evidence on the effectiveness and feasibility of robotic interventions in the field of hand therapy and upper limb rehabilitation.

## **2.0 PROBLEM STATEMENT**

Most patients recovered from wrist fracture, particularly the distal radius fracture have some residual disability or pain. MacDermid et al. (2003) found that at one year following distal radius fracture, of 129 patients, there were still 46% of them experienced certain extent of difficulty with usual activities, ranging from very severe to mild. Although majority of recovery following a distal radius fracture occurred within six-months after conventional hand therapy regime, most of the patients can be expected

to still experience minimal pain and disability. Distal radius fracture cases can take up to few months and one or two years to achieve maximal functional improvement (Michlovitz et al., 2001). The residual disability or pain, along with the long functional recovery period following distal radius fracture may impact the socioeconomics of a person, family, and society significantly. With the advancement in rehabilitation technology, robotic intervention had shown positive outcomes in neurological rehabilitation programme for the past decades. However, there is a lacking of published evidence about the feasibility and effectiveness of robotic intervention in orthopaedic rehabilitation programme, especially in the field of hand therapy.

## **2.1 RESEARCH JUSTIFICATION**

Upper limb robotic interventions have shown promising results and positive evidence in functional recovery of the neurological population. Robotic interventions are capable to provide highly repetitive, intensive, and task-specific training required for functional restoration based on current concepts of motor learning, practiced-induce neuroplasticity and muscle plasticity. Currently, there are vast of studies on the clinical applications of robotic interventions for neurological rehabilitation. However, the use of robotic interventions in orthopaedic rehabilitation especially for the wrist and hand remains inadequately explored. This study aims to determine the effectiveness of robotic interventions in improving the functions as well as the recovery period following distal radius fracture.

## **2.2 RESEARCH QUESTION**

Does a combined conventional therapy with Single Joint Hybrid Assistive Limb (HAL-SJ) robotic therapy provide greater effectiveness in improving functional level, physical performance and work readiness among workers with wrist fractures compared to conventional therapy alone?

## **2.3 HYPOTHESIS**

Hypothesis 1: A 4-week combined conventional therapy and Single Joint Hybrid Assistive Limb (HAL-SJ) robotic therapy provides greater functional level improvement among workers with wrist fractures as compared to those receiving conventional therapy alone during the same intervention period as measured by the Disabilities of the Arm, Shoulder, and Hand (DASH) Outcome Measure.

Hypothesis 2: A 4-week combined conventional therapy and Single Joint Hybrid Assistive Limb (HAL-SJ) robotic therapy provides greater improvement in term of pain reduction among workers with wrist fractures as compared to those who only receive standard conventional therapy in the same intervention period as measured by the Visual Analogue Scale (VAS).

Hypothesis 3: A 4-week combined conventional therapy and Single Joint Hybrid Assistive Limb (HAL-SJ) robotic therapy provides greater improvement in term of wrist and fingers range of motion among workers with wrist fractures as compared to those who only receive standard conventional therapy in the same intervention period as measured by the goniometer.

Hypothesis 4: A 4-week combined conventional therapy and Single Joint Hybrid Assistive Limb (HAL-SJ) robotic therapy provides greater improvement in term of grip strength among workers with wrist fractures as compared to those who only receive standard conventional therapy in the same intervention period as measured by the Jamar dynamometer.

Hypothesis 5: A 4-week combined conventional therapy and Single Joint Hybrid Assistive Limb (HAL-SJ) robotic therapy provides greater improvement in term of pinch strength among workers with wrist fractures as compared to those who only receive standard conventional therapy in the same intervention period as measured by the B&L Engineering pinch gauge.

Hypothesis 6: A 4-week combined conventional therapy and Single Joint Hybrid Assistive Limb (HAL-SJ) robotic therapy provides greater improvement in term of fine dexterity of hand function among workers with wrist fractures as compared to those who only receive standard conventional therapy in the same intervention period as measured by the Purdue Pegboard Test.

Hypothesis 7: A 4-week combined conventional therapy and Single Joint Hybrid Assistive Limb (HAL-SJ) robotic therapy provides greater improvement in term of gross dexterity of hand function among workers with wrist fractures as compared to those who only receive standard conventional therapy in the same intervention period as measured by the Box and Block Test.

Hypothesis 8: A 4-week combined conventional therapy and Single Joint Hybrid Assistive Limb (HAL-SJ) robotic therapy provides greater improvement in work readiness among workers with wrist fractures as compared to those receiving conventional therapy alone during the same intervention period as measured by the Lam Assessment of Stages of Employment Readiness (LASER).

## **2.4 RESEARCH OBJECTIVE**

### **2.4.1 General Objective**

The objective of this research is to determine the effectiveness of Single Joint Hybrid Assistive Limb (HAL-SJ) robotic therapy in improving functional level, physical performance, and work readiness among workers with wrist fractures after 4 weeks of intervention.

### **2.4.2 Specific Objective**

a. Specific objective 1:

To determine the effectiveness of Single Joint Hybrid Assistive Limb (HAL-SJ) robotic therapy on functional level among workers with wrist fracture after 4 weeks of intervention.

c. Specific objective 2:

To determine the effectiveness of Single Joint Hybrid Assistive Limb (HAL-SJ) robotic therapy on physical performance in terms of pain level, wrist and fingers range of motion, grip and pinch strength as well as hand dexterity among workers with wrist fracture after 4 weeks of intervention.

d. Specific objective 3:

To determine the effectiveness of Single Joint Hybrid Assistive Limb (HAL-SJ) robotic therapy on work readiness among workers with wrist fracture after 4 weeks of intervention.

## 2.5 CONCEPTUAL FRAMEWORK

[figure not shown]

### **3.0 METHODOLOGY**

#### **3.1 STUDY DESIGN**

This research will use a randomized controlled trial (RCT) design where the effects of the study treatment (intervention) are compared with those of a control treatment after the patients were being randomly assigned to the two groups i.e., the control group and the intervention group.

#### **3.2 STUDY POPULATION**

The target participants are Social Security Organisation (SOCSO) insured workers with wrist fractures that match both the inclusion and exclusion criteria and receiving rehabilitation management at PERKESO Rehabilitation Centre. The PERKESO Rehabilitation Centre is selected in this study because the researcher is working at this facility which provides convenience for him to carry out the research and intervention for the participants. In addition, PERKESO Rehabilitation Centre is a subsidiary body under SOCSO that appears to be one of the largest rehabilitation facilities in Malaysia. It plays a vital role in providing free comprehensive and intensive rehabilitation program to all injured workers covered under the SOCSO scheme.

#### **3.3 SAMPLE SIZE**

The sample size of each hypothesis is calculated by using the G\* power analysis. Given that this is a novel study and there is no reference from previous study, sample size was calculated using ANOVA repeated measures, within-between interaction with Cohen-f effect size at 0.25 for a medium effect, alpha error at 0.05 and 80% power. Result showed that a total of 34 participants will be needed. By adding 10% dropout rate, the required sample size became 38 participants.

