and those who were not (26.8 vs. 50.7,  $t=-7.51$ ,  $p<0.0001$ ) as well as patients who were functioning and the scores of those who were not (23.6 vs. 47.1,  $t=-5.81$ ,  $p<0.0001$ ). The DASH is responsive to the different types of change before and after treatment of the target conditions (Standardized Response Mean, SRM=0.74-0.80) and in those patients whose ability to function had improved (SRM=0.92-1.40). The Malay version of DASH has internal consistency, Cronbach's  $\alpha$  0.99 and test-retest reliability, ICC=0.94 (Al-Husunny et al. 2011). The DASH Outcome Measure that will be used (English, Malay, and Chinese versions) are attached as Appendices C, D and E.

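### Section 3.3 calls f = 0.25 a medium effect, but for this two-arm, two-visit interaction it is a 1.0 SD between-arm difference in change; power for 0.5 SD is about 29% at the implied correlation of 0.5 (22% to 61% for correlations 0.3 to 0.8)

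*Combined protocol and SAP*

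**What the plan says.** Section 3.3 opens by explaining why a conventional effect size is used: "Given that this is a novel study and there is no reference from previous study". It then names a repeated-measures ANOVA as the method and gives its inputs: "within-between interaction with Cohen-f effect size at 0.25 for a medium effect, alpha error at 0.05 and 80% power". The outcome is "Result showed that a total of 34 participants will be needed", followed by "By adding 10% dropout rate, the required sample size became 38 participants". The calculation is presented as applying to every hypothesis, and section 2.3 lists eight.

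The design that fixes the other inputs is described elsewhere. Section 3.1 has two groups. Section 3.5, item g, uses equal numbers of allocation cards for the two arms. Section 3.8 tests each hypothesis with a mixed model ANOVA on two measurements, baseline and 4 weeks.

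Section 3.3 gives no correlation between the two measurements, no SD, and no target difference in DASH points or any other outcome unit. The word medium is therefore its only description of how large a benefit the trial is built to detect.

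**The concern.** Cohen's f has no fixed meaning across designs. In a comparison of two independent groups, d = 2f, so f = 0.25 corresponds to d = 0.5, the conventional medium effect. In a 2x2 interaction the same f spreads the difference in change over four cells, and the between-arm difference is four times f. Carrying the label from the first setting to the second doubles the difference that the trial needs to see.

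At stake is how the trial's sensitivity is understood. Someone reading section 3.3 would take it that a benefit of moderate size has an 80% chance of being detected on each of the eight hypotheses. If the calculation targets a 1.0 SD difference in change, the chance for a benefit half that size is far lower.

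**Working it through.** **Inputs.** From section 3.3: f = 0.25, alpha = 0.05, power 80%, N = 34, dropout 10%. From sections 3.1, 3.5 and 3.8: k = 2 groups, equal allocation (17 per arm), m = 2 measurements. Not in the documents: the correlation rho between baseline and week 4. It is assumed to be 0.5 to start with, then varied.

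**Step 1: reproduce the plan's figure.** For the within-between interaction, with f defined in SDs of the outcome at a single time point:

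lambda = f² × N × m / (1 − rho), df1 = (k − 1)(m − 1) = 1, df2 = (N − k)(m − 1) = N − 2.

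With N = 34 and rho = 0.5, lambda = 0.0625 × 34 × 2 / 0.5 = 8.5 on 1 and 32 df. Power is 80.7%. At N = 32 it is 78.1%, so 34 is the smallest balanced total. For dropout, 34/0.9 = 37.8 and 34 × 1.1 = 37.4; both round up to 38. The plan's numbers stand.

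The same f with two visits gives other totals at other correlations: 46 at rho = 0.3, 40 at 0.4, 28 at 0.6 and 22 at 0.7. Three visits at rho = 0.5 would give 28. The stated 34 therefore points to rho = 0.5 as the value used.

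**Step 2: translate f into a difference between arms.** Take cell means 0 and 0 for control (baseline, week 4) and 0 and D for the robot arm. After removing row and column effects, each cell's interaction effect is ±D/4. Hence f = D/(4 SD), and D = 4f × SD = 4 × 0.25 = 1.0 SD of the outcome at a single time point. This holds at any rho.

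The SD of change is SD × √(2(1 − rho)). At rho = 0.5 this equals the time-point SD, so the target is also 1.0 SD of change.

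*Check.* A 1-df interaction with two visits is the two-sample t-test on change scores. With d = 1.0 SD of change and 17 per arm, its power is 80.7% (80.9% in 40,000 simulated trials), matching step 1.

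**Step 3: power for half that difference.** A difference of 0.5 time-point SD is f = 0.125. At rho = 0.5, lambda = 0.015625 × 34 × 2 / 0.5 = 2.125, and power is 29.3% (simulation 29.3%). If all 38 are evaluable it is 32.3%. Reaching 80% would take 128 evaluable participants. A plain two-group comparison at d = 0.5, the setting to which the medium label belongs, also needs 128.

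**Step 4: vary the unstated correlation** (N = 34, two-sided 0.05, differences in time-point SDs).

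| rho | Power for 0.5 SD (f = 0.125) |
|---|---|
| 0.3 | 22% |
| 0.5 | 29% |
| 0.6 | 35% |
| 0.7 | 45% |
| 0.8 | 61% |

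At rho = 0.3, the stated f = 0.25 gives lambda = 0.0625 × 34 × 2 / 0.7 = 6.07 and power of 67%.

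**The case against.** The best defence is that section 3.3 contains no arithmetic error. It claims 80% power for f = 0.25, and that is true for its inputs. The documents never define medium as 0.5 SD. This stands: the plan makes no explicit claim of 80% power for 0.5 SD, and the fault lies in the label. But the section offers no other description of its target, and 1.0 SD is not what the label conveys.

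A second objection is that 29% depends on a correlation the documents do not give. This also stands, so the figure needs its range. The direction is unaffected: power for 0.5 time-point SD stays below 80% for every correlation from 0.3 to 0.8.

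Two stronger readings are tempting, and the documents do not support either.

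- A reader might set the 1.0 SD target against the DASH responsiveness figures in section 3.6.3, "before and after treatment of the target conditions (Standardized Response Mean, SRM=0.74-0.80", and conclude that the robot arm must gain about 2.3 times as much as control: (0.74 + 1)/0.74 = 2.35 and (0.80 + 1)/0.80 = 2.25. Those figures are in SDs of change, so adding them to a time-point SD is valid only at rho = 0.5. They also come from a different cohort and cannot be taken as the gain of this control arm, which has two 90-minute sessions each working day. They concern one outcome of eight hypotheses. The comparison is illustrative at most.
- A reader might infer that non-significant results will be reported as ruling out a medium benefit. Nothing in sections 2.3 or 3.8 says so; the hypotheses are of superiority, and there is no rule for concluding no effect.

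**Conclusion.** The point holds as a misdescription of the trial's sensitivity. N = 34 and N = 38 are right for f = 0.25 with two groups, two visits and a correlation of 0.5. What that f represents here is a 1.0 time-point SD difference in change, twice the difference that the medium label implies.

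The size of the gap rests on two assumptions: that medium is read as the two-group equivalent of f = 0.25, and that the correlation lies between 0.3 and 0.8. The 1.0 SD translation needs neither. A separate consequence of leaving the correlation unstated is that the 80% figure for f = 0.25 is itself conditional, and is lost if the true correlation is well below 0.5.

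**What to change.** Keep N = 38. In section 3.3, delete the description of f = 0.25 as medium and restate the claim along these lines:

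> With 34 evaluable participants (two-sided alpha 0.05, assumed baseline/week-4 correlation 0.5) the trial has about 80% power to detect a between-group difference in change of 1.0 SD (SD of the outcome at a single time point, equal to the SD of change at this correlation). Power for 0.5 SD is about 29% (22% to 61% for correlations from 0.3 to 0.8).

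In section 3.8, add that between-group differences will be reported with 95% confidence intervals. If the team can justify a target in outcome units with its SD, adding it would help, but the correction does not depend on it.

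The cost is one paragraph in section 3.3 and a sentence in section 3.8. No participants, visits or tests change. The downside is a less favourable stated sensitivity.
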